#### Individual-level cohorts

Individual-level ITT and PP cohorts will only include children enrolled as infants at EPI clinics to receive the study intervention. The individual-level ITT cohort will be used to calculate the prevalence of VT pneumococcal carriage in resident study participants presenting with clinical pneumonia in year 4. The individual-level ITT cohort will include all resident participants enrolled to receive study interventions who present with clinical pneumonia, assigning them to the study groups according to the allocation of their village of residence at enrolment, regardless of age at enrolment, the schedule, or number of doses received. The denominator in prevalence calculations will be the number of eligible children with clinical pneumonia. Repeated events in one individual will be included with the related non-independence of events accounted for in the cluster-level effect included in the GEE model.

The individual-level PP cohort will be used to calculate the prevalence of VT pneumococcal carriage in study participants presenting with clinical pneumonia in year 4. The individual-level PP cohort will include fully vaccinated resident participants (see the ‘Definition and assessment of adherence to the intervention’ section), enrolled at ≤273 days of age who present with clinical pneumonia, assigning them to the study groups according to the village of residence at enrolment. The denominator in prevalence calculations will be the number of eligible children with clinical pneumonia in the individual-level PP cohort. Repeated events will be included.

Incidence endpoints will be analysed using the individual-level ITT cohort including all participants enrolled to receive the intervention, assigning them to the study groups according to the allocation of their village of residence at enrolment, regardless of age at enrolment, the schedule, or number of doses received. Event counting starts on the date of enrolment. Follow-up ends either at death, outmigration, or the end of the follow-up period, whichever is earlier.

Incidence endpoints will also be analysed using the individual-level PP cohort including participants enrolled to receive the intervention, enrolled at ≤273 days of age, are fully vaccinated (see the ‘Definition and assessment of adherence to the intervention’ section), assigning them to a study group according to the village of residence at enrolment. Event counting starts 14 days after the administration of the first dose of PCV. Follow-up ends either at death, migration out of the HDSS, or the end of the follow-up period, whichever is earlier.

Individual-level cohort analyses using ITT and PP cohorts will calculate the incidence of radiological pneumonia and VT IPD. VT IPD is the most specific endpoint able to detect potentially differential efficacy of the two schedules; however, small numbers of events will limit the power to detect differences. Radiological pneumonia is an endpoint of unknown, but likely only modest specificity, and may be able to detect differences between the schedules. Although numbers of events are significant, the number is limited and may not have sufficient power to detect differences. Individual-level analyses using ITT and PP cohorts will also calculate the incidence of clinical pneumonia, hypoxic pneumonia, clinical pneumonia associated with NP carriage of VT, NVT, any pneumococci, hospitalisation, mortality, non-pneumococcal bacteraemia, and diarrhoea.

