### Adherence and protocol deviations

#### Definition and assessment of adherence to the intervention

##### Vaccination status—per-protocol

Vaccination per-protocol (PP) will be defined as a child enrolled into the study at ≤273 days (≤40 weeks) of age and who received the allocated schedule of PCV doses during follow-up. PP administration of the standard schedule of three doses will require allocation to the standard schedule and administration of three doses of PCV at ≤152 days (≤22 weeks) of age. PP administration of the alternative schedule will require administration of two doses of PCV, the first dose ≤152 days (≤22 weeks) of age, and administration of the second dose ≥273 days (≥40 weeks) and ≤365 days (≤52 weeks) of age.

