##### Vaccination status—cross-over

Participants resident in a village allocated to the standard schedule will be defined as cross-over between groups if doses of PCV are received at an age when a dose will function as a booster, as is the intention of the alternative schedule. For infants allocated to the standard schedule, cross-over is defined as administration of (a) two doses of PCV with the second dose administered at ≥252 days (≥36 weeks) of age with an interval of >152 days (>21 weeks), or (b) three doses of PCV with the third dose administered at ≥252 days (≥36 weeks) of age with an interval of >152 days (>21 weeks) between the first and third doses, or (c) four doses of PCV with the fourth dose administered at ≥252 days (≥36 weeks) of age.

The definition of cross-over for infants resident in a village allocated to the alternative schedule is related to receiving three or more doses of PCV at an age when doses will not function as a booster, as is the intention of the standard schedule. For infants allocated to the alternative schedule, cross-over is defined as the administration of (a) three doses of PCV with the administration of the third dose <252 days (<36 weeks) of age, or (b) four doses with the administration of the fourth dose <252 days (<36 weeks) of age. Infants that migrate internally between clusters with alternate group allocation, before completing their PCV schedule, may validly change group allocation to the destination cluster. Internal migrations between clusters with alternate group allocation after completing their PCV schedule will be classified as cross-overs from the time of the migration.

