##### Assessment of individual-level adherence

Individual-level adherence will be assessed as (a) PP vaccination, (b) ITT vaccination, (c) incomplete vaccination, (d) cross-over, (e) unvaccinated, or (f) migration/death before completion. Individual-level adherence will be assessed cumulatively over the 4 years of intervention and reported as proportions of participants enrolled at EPI clinics who fall into these mutually exclusive categories.

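### The SAP's rules conflict on how the per-protocol cohort treats children who move between arms: status can follow one allocation while the analysis arm follows another, and cross-over time is not cut

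*SAP article*

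**What the plan says.** Four parts of the SAP article bear on an enrolled child who moves between clusters of opposite allocation.

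- **Vaccination status—per-protocol.** A per-protocol child is one "who received the allocated schedule of PCV doses during follow-up". For the standard arm the SAP adds that "PP administration of the standard schedule of three doses will require allocation to the standard schedule", with all three doses by 152 days. The alternative rule lists only dose number and ages: two doses, the first by 152 days and the second at 273 to 365 days.
- **Vaccination status—cross-over.** An infant who moves before completing PCV "may validly change group allocation to the destination cluster". Children who move after completing it "will be classified as cross-overs from the time of the migration".
- **Assessment of individual-level adherence.** Per-protocol and cross-over are separate classes, and participants "fall into these mutually exclusive categories".
- **Individual-level cohorts.** For per-protocol carriage prevalence the plan is "assigning them to the study groups according to the village of residence at enrolment"; for per-protocol incidence it is "assigning them to a study group according to the village of residence at enrolment". Neither makes an exception for a valid change of allocation. For incidence, "Follow-up ends either at death, migration out of the HDSS, or the end of the follow-up period, whichever is earlier". A move between arms inside the surveillance area is not on that list.

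**The concern.** A per-protocol cohort is defined by the schedule received, so the allocation used to judge receipt should also name the arm. Here the two can differ. The enrolment-village rule suits the ITT cohort. Carried over unchanged to the per-protocol cohort, it can put a child who validly completed one schedule into the arm of the other.

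The per-protocol results have a specific job. Background and rationale presents the individual-level analyses as informing the biological effects and relative safety of the schedules, and the per-protocol results as the easiest to compare between sites. The safety text under Additional analyses uses the ITT and per-protocol cohorts for VT IPD, radiological pneumonia and mortality. The comparison before and after the booster is restricted to per-protocol children, and receipt of the second dose defines its time windows, so a wrong arm label matters directly there. Mixing schedules moves a ratio towards 1, which is the unsafe direction when the question is harm. An unsettled rule also leaves a choice to be made after data are seen, which the SAP says early specification is meant to prevent.

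**Working it through.** The SAP gives no figure to reproduce on this point, so the check sets the rules side by side and then sizes the possible effect under stated assumptions.

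**1. Child who moves early, standard to alternative.** Enrolled in a standard village, dose 1 at 42 days, moves to an alternative village, dose 2 at 273 days.

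- *Allocation follows the move:* two doses, the first by 152 days and the second between 273 and 365 days. The child meets the alternative per-protocol rule, but Individual-level cohorts counts the child in the standard arm.
- *Allocation stays at enrolment:* the child lacks three doses by 152 days. The second dose is at or after 252 days and the interval is 273 − 42 = 231 days, which exceeds 152, so the child is a cross-over and not per-protocol. No mixing occurs, but the valid change of allocation then has no effect in this analysis.

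**2. Child who moves early, alternative to standard.** Dose 1, a move, then three doses in all by 152 days.

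- *Allocation follows the move:* standard per-protocol, analysed in the alternative arm.
- *Allocation stays at enrolment:* third dose before 252 days, so a cross-over.

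In both directions the same child falls into one or the other of two classes declared mutually exclusive, depending on a word the SAP does not define.

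**3. Child who moves after completing PCV.** The child received the enrolment arm's doses and is properly per-protocol up to the move. From then on the cross-over section gives one label, while the follow-up rule keeps the time in the per-protocol analysis. What changes at the move is the surrounding transmission (indirect effects), not the doses.

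**4. How long the early-mover window is.** In case 1 the child must have had exactly one dose at the move. On schedule (doses at 6 and 10 weeks) that is 10 − 6 = 4 weeks, longer if dose 2 is late. In case 2, keeping the scheduled four-week spacing, dose 2 must be given by 152 − 28 = 124 days. With dose 1 at 42 days the window is at most 124 − 42 = 82 days. The child must then also comply fully with the destination schedule. For case 3 the window stays open for the rest of follow-up.

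**5. Size, for early movers only and only if allocation follows the move.** Let R be the true incidence ratio and m the share of each per-protocol arm's person-time under the other schedule. The SAP gives no m; it is assumed here, equal in both arms, with mixed time carrying the other schedule's full rate.

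Observed ratio = ((1 − m)R + m) / ((1 − m) + mR)

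For R = 1.30 and m = 0.02: (0.98 × 1.30 + 0.02) / (0.98 + 0.02 × 1.30) = 1.294 / 1.006 = 1.286.

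| True R | m = 1% | m = 2% | m = 5% | m = 10% |
|---|---|---|---|---|
| 1.30 | 1.293 | 1.286 | 1.266 | 1.233 |
| 2.0 | 1.970 | 1.941 | 1.857 | 1.727 |

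The windows in step 4 point to the left of the table. The formula does not describe case 3.

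**The case against.** The strongest reply is that the text can be read without any mixing. If *allocated* means allocated at enrolment, in line with the arm rule in Individual-level cohorts, the early mover fails the per-protocol rule, becomes a cross-over and drops out. This is a possible reading, and it means mixing cannot be asserted as a fact. It does not remove the problem: the cross-over section says in plain terms that allocation may change, and nothing says that the per-protocol definition ignores the change.

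A reader might infer that each per-protocol arm certainly contains the other schedule, and that late movers add to this. The documents do not support that. For early movers it depends on the unsettled reading. Late movers had their own arm's doses, so their later time brings only the other arm's indirect effects.

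The consequence is also limited. Table 1 lists the per-protocol analyses as tertiary. Individual-level incidence analyses follow the population-level methods, where the SAP says no hypothesis is tested. ITT results stand beside them, and internal migrations are to be tabulated with and without cross-over. All of this stands, and it keeps the point modest.

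Finally, censoring at an internal move has its own risk, since movers may differ from those who stay. That is fair and is a cost of the fix. But the SAP already classes this time as cross-over, so the two rules need reconciling whichever is kept. Simply relabelling early movers by the schedule completed would be wrong, because counting starts 14 days after dose 1 and pre-move events would be credited to the destination arm.

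**Conclusion.** The point holds as a conflict between stated rules. The SAP does not settle which allocation decides per-protocol status for a child who moves before completing PCV. On the plain sense of the cross-over section, such a child can be per-protocol on one schedule and analysed in the arm of the other. Separately, time that the SAP labels cross-over stays in per-protocol follow-up.

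The size is unknown because the number of between-arm moves is not given. It is probably small: the early-mover windows are a matter of weeks, and at an assumed 1% to 2% a true ratio of 1.30 would read 1.29. The 5% and 10% columns only show direction and scale; nothing in the SAP supports shares that high. Any mixing biases tertiary and safety per-protocol ratios towards 1. The primary endpoint, analysed in all resident children with clinical pneumonia whatever doses they received, is not affected.

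**What to change.** Change the per-protocol cohort only, and keep enrolment village for ITT.

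1. State that the allocation defining per-protocol status is also the one that sets the analysis arm. Either of two rules does this:
   - exclude children whose completed schedule is not that of their enrolment village; or
   - analyse children with a valid change of allocation in the destination arm, with time and events counted only from the move.

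   The first is simpler and keeps assignment by randomised enrolment village. The second keeps more children.
2. Add to the per-protocol follow-up rule that it ends on the date of a move classed as cross-over in the cross-over section.
3. Use the same wording in the per-protocol definition, the cross-over section and Individual-level cohorts, so that each child has one class and one arm at any time.

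The cost is a few lines of SAP text. Internal migrations, with and without cross-over, are already to be summarised under Descriptive analysis of the surveillance population. The price in the analysis is a small loss of per-protocol children and person-time, and censoring at the move that could be mildly informative.

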	“	“	Clinical pneumonia	“
	“	“	Clinical pneumonia and VT carriage	“
	“	“	Hypoxic pneumonia	“
	“	“	Hospitalisation	“
	“	“	Mortality	
	Enrolled children received intervention	^j^Per-protocol	Radiological pneumonia	“
	“	“	VT, NVT, and Spn IPD	“
	“	“	Clinical pneumonia	“
	“	“	Clinical pneumonia and VT carriage	“
	“	“	Hypoxic pneumonia	“
	“	“	Hospitalisation	“
	“	“	Mortality	“

^a^Population-based population aged 2–260 weeks. ^b^Primary endpoint specified in year 4 and also calculated as tertiary endpoints in years 1, 2, and 3. ^c^Cohort enrolled to receive interventions. ^d^Events counted from enrolment to end of follow-up. ^e^Secondary endpoint specified in year 4 and also calculated as a tertiary endpoint in year 3 (all ages and age-stratified). ^f^Calculated in years 1, 2, 3, and 4. ^g^Spn = all pneumococcal carriage. ^h^In year 4. ^i^Cohort enrolled and received interventions PP. ^j^Events counted from 14 days post-PCV1 to end of follow-up

The trial includes two secondary endpoints (Table 1). The secondary endpoint of radiological pneumonia incidence will include all children enrolled to receive the interventions and function primarily as a safety endpoint. This individual-level cohort will experience the direct effects of the different PCV schedules and their increasing indirect effects over 4 years. The radiological pneumonia endpoint offers reasonable specificity [9] to detect a potential difference in the incidence of this important disease endpoint. However, limited frequency and statistical power precludes specification of a non-inferiority hypothesis for this endpoint. We will present a point estimate and confidence interval indicating the potential range of values of the incidence rate ratio of radiological pneumonia in the two groups. An additional secondary endpoint will be VT pneumococcal carriage at the community-level in all ages in year 4. This population-level measurement of VT carriage will include direct and indirect effects after 4 years of intervention delivery in the population.

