##### Vaccination status—out-migration or death before age to complete vaccination

Vaccination status in individual-level analyses will be defined as out-migration or death before age to complete if the child migrates out at an age before which their PCV schedule could reasonably be completed. Infants resident in standard schedule villages who out-migrate or die before age ≤112 days (16 weeks) and receive zero doses of PCV will be classified as ‘standard schedule, out-migration/death, unvaccinated before age 16 weeks’ and ‘standard schedule, out-migration/death, incomplete before age 16 weeks’ if one or two doses are received. Infants resident in alternative schedule villages who out-migrate or die before age ≤294 days (≤42 weeks) and receive zero doses of PCV will be classified as ‘alternative schedule, out-migration/death, unvaccinated before age 42 weeks’ and ‘alternative schedule, out-migration/death, complete before age 42 weeks’ if one dose of PCV is received.

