### Additional analyses

Analysis of the primary endpoint using data from year 2 of intervention (1 Nov 2020–31 Oct 2021) will be conducted with a superiority hypothesis, aiming to detect potential early effects of the interventions. The statistical model will estimate the prevalence difference (and 95% CI). Interpretation will be based on the a priori statement that the smallest significant difference is prevalence ratio of 1.47.

Analysis will include group-wise calculation of the intra-cluster correlation coefficients for VT pneumococcal carriage in children with clinical pneumonia, population-based carriage survey in year 4, and the survey of carriage in young infants in year 4.

We will explore potential differential risk of events in the alternative schedule group before and after administration of the booster dose. We will calculate incidence rate ratios for radiological pneumonia and hypoxic pneumonia among those who received PCV per-protocol (see the ‘Definition and assessment of adherence to the intervention’ section). We will count events from 14 days after administration of the first dose of PCV, before administration of the second dose (alternative schedule group), and ≤288 days of age (9 months and 2 weeks). We will also count events from 7 days after administration of the second dose of PCV (alternative schedule group) and >288 days of age. These analyses will isolate the period of potential inferiority before the booster dose in the alternative schedule group.

*Safety*

PCV13 is a licensed product with an excellent safety profile. Safety at the individual level is best evaluated by comparison of infants enrolled at EPI clinics to receive the trial intervention schedules. In these safety analyses, the effects of the two schedules will not be diluted by the inclusion of children who may not have been enrolled to receive the interventions, as is done in population-level analyses. Thus, any differences between the two schedules will be more likely detected in these individual-level analyses. Individual-level ITT and PP safety analyses will include the endpoints of VT IPD, radiological pneumonia, and mortality incidence (see the ‘Individual-level cohort incidence endpoints’ section).

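### Per-protocol incidence starts 14 days after dose 1 but admits only children who complete their schedule later, which biases per-protocol mortality in favour of the alternative schedule

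*SAP article*

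**What the plan says.** *Individual-level cohorts* restricts the PP incidence cohort to fully vaccinated children and then states: "Event counting starts 14 days after the administration of the first dose of PCV". The Table 1 footnote agrees: "Events counted from 14 days post-PCV1 to end of follow-up".

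Full vaccination is defined under *Vaccination status—per-protocol* as a child "who received the allocated schedule of PCV doses during follow-up". In the standard group this means "administration of three doses of PCV at ≤152 days (≤22 weeks) of age". In the alternative group it means a first dose by day 152 and "administration of the second dose ≥273 days (≥40 weeks) and ≤365 days (≤52 weeks) of age".

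*Assessment of individual-level adherence* makes migration or death before completion a category of its own, mutually exclusive of PP. The section defining that category uses cut-offs of 112 days (16 weeks) for the standard group and 294 days (42 weeks) for the alternative group.

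*Additional analyses* adds a comparison before and after the booster: "We will calculate incidence rate ratios for radiological pneumonia and hypoxic pneumonia among those who received PCV per-protocol". Its early window is limited to time "before administration of the second dose (alternative schedule group), and ≤288 days of age". Its late window starts 7 days after the second dose and above 288 days of age. The same section names ITT and PP analyses of vaccine-type invasive pneumococcal disease (IPD), radiological pneumonia and mortality as the safety analyses. *Sensitivity analyses* plans none.

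**The concern.** Cohort membership is decided by events that happen after the clock starts, and for far longer in one arm. A death at 30 weeks counts in the standard PP cohort. The same death in the alternative group cannot count, because that child never receives the second dose and so is never PP. The alternative cohort nevertheless keeps the early person-time of every child who did survive to the booster. This is immortal time, unequal between arms, and it lowers the alternative group's rate.

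The stake is the PP half of the safety analyses, and above all the months between the first dose and the booster, when the SAP itself sees potential inferiority of the alternative schedule. A bias in that direction could hide harm.

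**Working it through.** The SAP states no expected PP rate or ratio, so there is no figure to reproduce. The check sizes the bias when true mortality is the same in both arms.

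**1. Guaranteed survival inside counted time**

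Formula: age at the last qualifying dose − (age at dose 1 + 14 days). Ages are from *Trial design* and *Vaccination status—per-protocol*.

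- Alternative, on schedule (day 42, then 273): 273 − 56 = 217 days. Range: 273 − (152 + 14) = 107 to 365 − (42 + 14) = 309.
- Standard, on schedule (days 42, 70, 98): 98 − 56 = 42 days. With dose 3 at day 152: 152 − 56 = 96.
- Difference on schedule: 217 − 42 = 175 days. For any shared age at dose 1, it is at least 273 − 152 = 121 days.

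**2. Null mortality ratio, constant hazard**

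Formula: (T − 217)/(T − 42), where T is days of counted follow-up per child.

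| Follow-up | Calculation | Ratio |
|---|---|---|
| 1 year | 148/323 | 0.46 |
| 2 years | 513/688 | 0.75 |
| 3 years | 878/1053 | 0.83 |
| 4 years | 1244/1419 | 0.88 |

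**3. Null mortality ratio, higher mortality in infancy**

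Assumptions, none of them from the SAP: counting starts at day 70; no countable death before day 126 (standard) or day 287 (alternative); rate h1 to day 365 and h2 after; follow-up F from day 70. Days after 365 are F − 295.

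Formula: [78·h1 + (F − 295)·h2] / [239·h1 + (F − 295)·h2], since 365 − 287 = 78 and 365 − 126 = 239. Rates are per 1000 child-years.

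- Lowest: h1 = 30, h2 = 4, F = 548 (1.5 years): (2340 + 1012)/(7170 + 1012) = 0.41.
- Middle: h1 = 20, h2 = 6, F = 548: (1560 + 1518)/(4780 + 1518) = 0.49.
- Highest: h1 = 12, h2 = 10, F = 913 (2.5 years): (936 + 6180)/(2868 + 6180) = 0.79.

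Deaths that cannot be counted, per 1000 infants at 12-30 per 1000 child-years:

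- Alternative, 217 days: about 7-18.
- Standard, 56 days: about 2-5.
- Net, 161 days: about 5-13.

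**4. Simulation**

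Two million children per arm, identical mortality, enrolment spread over 4 years, dose 1 at days 42-70, booster at days 273-310, standard dose 3 at dose 1 + 56 days. Assumed yearly mortality (infancy/later) and the resulting PP ratio:

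- 1%/1%: 0.77
- 2%/1%: 0.65
- 2%/0.4%: 0.50
- 3%/0.5%: 0.46

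Starting both arms at day 365 returns the ratio to 0.99-1.01.

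**5. The 288-day boundary in the pre-booster analysis**

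A child boosted on day 365 enters the late window at day 372, so 372 − 288 = 84 days fall in neither window. A child boosted on day 273 loses only the days from the booster to day 288, about two weeks. Standard-group time passes from one window to the other without a gap.

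**The case against.** **The SAP offers little rescue.** A one-dose alternative-group child who leaves or dies before 42 weeks is labelled complete in one category name, but PP still requires two doses. *Individual-level cohort incidence endpoints* borrows its person-time rule from the population-level section, where time runs from birth. That conflicts with *Individual-level cohorts* and would lengthen the event-free time.

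**What stands on the other side.** PP incidence is tertiary and tests no hypothesis. The safety analyses are specified as ITT and PP together. ITT counts from enrolment regardless of doses and covers the same endpoints, including radiological pneumonia as a secondary endpoint. Deaths and migrations before completion will be tabulated by group, so the exclusions will be visible. No non-inferiority conclusion rests on PP incidence. On the other hand, no ITT version of the pre-booster analysis is specified.

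**Stronger readings that the document does not support.**

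- A reader might apply the mortality ratios to radiological pneumonia, IPD or hospitalisation. A non-fatal event before the booster still counts if the child is boosted by day 365, so the bias there is selection on surviving, staying and attending. It is smaller and not quantified.
- A reader might infer the same defect in PP carriage prevalence in year 4, on the ground that young alternative-group infants cannot be PP. That treats PP as status at presentation, whereas the definition reads as final status: an infant swabbed at 20 weeks and boosted on time is PP. A prevalence also has no person-time.
- The 84-day gap is a maximum. One age boundary for both arms has a purpose, since the standard group has no booster date, and nothing shows which arm the gap favours.

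**Conclusion.** The concern holds for PP mortality. As written, the rule pushes the ratio below 1 under equal true mortality and so favours the alternative schedule. The direction follows from the SAP's own dose windows. The size rests on assumed mortality and follow-up: about 0.41-0.79 under the infancy-weighted assumptions, and about 0.75-0.88 under a constant hazard with 2-4 years of follow-up. The other PP incidence endpoints carry a lesser selection bias. So does the pre-booster analysis, which covers radiological and hypoxic pneumonia rather than mortality and also leaves some alternative-group time unassigned. The primary endpoint and all ITT incidence analyses, including the secondary radiological pneumonia endpoint, are untouched.

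**What to change.** 1. For PP mortality and the other PP incidence endpoints, choose one of two rules.
   - Start person-time in both groups at one common landmark age after both PP windows have closed (after day 365), among PP children alive and resident then.
   - Or enter every enrolled child with a qualifying first dose at dose 1 + 14 days, count all events while the child is on the allocated schedule, and censor at the first departure. State that this censoring may be informative, since illness can cause a missed dose, and that it can begin at day 152 in one arm and day 365 in the other.
2. Run the pre-booster analysis in all enrolled children with a qualifying first dose, without requiring later receipt of the booster. Compare the groups within the same age bands. Assign alternative-group time between day 289 and 7 days after the actual booster to the unboosted period.

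The cost is SAP wording and reprogramming, with no new data. The landmark drops early person-time and so cannot serve the pre-booster question. The censoring rule keeps that time but relies on an assumption about why children leave the schedule.
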